#### Dietary intake

Dietary intake data will be collected three times during pregnancy; at the end of the first trimester, the end of the second trimester and 1 month after delivery. We will use a validated Food Frequency Questionnaire (FFQ) with three months’ recall to collect the usual dietary intake of pregnant women. The FFQ used in the MSAKI study in India will be adopted and validated in the local settings before use in the main trail. Portion sizes of foods will be quantified using standard local utensils. Recipes used to prepare meals will be recorded, including amounts of raw food used and the preparation methods. The dietary interviewers will use the 24-h recall method for collecting child dietary intake information by recording all foods and the quantity consumed by the child in the 24 h before the interview. Our analysis will compare the nutrient density of the infant diets with the desired levels, and the percentage of mothers at risk of inadequate nutrient intakes will be estimated using the fixed cut-point approach with WHO/FAO estimated average nutrient requirements.

#### Food security

We will assess household food security using the World Food Program’s Food Insecurity Experience Scale, an indicator of household food access, which combines data on dietary diversity and food frequency using 12 months recall [37].

#### Child morbidity

At scheduled monthly visits, trained interviewers will record maternal recall of symptoms in the preceding 2 weeks of common childhood illnesses (diarrhoea, acute respiratory illnesses and fever) using standard questions from Bangladesh Demographic and Health Survey (BDHS) [4].

#### Women’s empowerment

We will collect data on women empowerment at the baseline and end-line assessments of the trial using the Project-Level Women’s Empowerment in Agriculture Index (Pro-WEAI) questionnaire [38]. We will develop a composite indicator based on the following: 1) control over the use of income; 2) input in production decisions; 3) autonomy in income; 4) decision making power about women and children’s health and nutrition; 5) respect among household members and 6) attitudes toward IPV. The Pro-WEAI is used to measure empowerment of women, agency and inclusion in the agriculture sector [38], is a standardised, survey-based internationally validated index, and has been piloted in Bangladesh [38, 39].

#### Intimate partner violence

The Pro-WEAI includes questions about a woman’s attitude to intimate partner violence (IPV). Further data collection is required to determine precisely how cash transfers and nutrition behaviour change communication affects IPV. The additional questions ask about the personal experience rather than the women’s perceptions of IPV. We will take the questions for this assessment from the Violence Against Women and Girls Survey (Bangladesh 2015) [40].

#### Maternal depression

To measure any change in postpartum depression, we will use the Centre for Epidemiological Studies Depression Scale (CES-D). This twenty item self-report measure screens women for symptoms of emotional distress during pregnancy and the postnatal period.

#### Social, economic and demographic characteristics

Data for social, economic and demographic characteristics will be collected in baseline questionnaires using Demographic and Health Survey methods which include an inventory of household assets to construct a wealth index [41] and the mother’s socio-demographic and reproductive characteristics.

#### Economic evaluation

We will conduct an economic evaluation, from the societal perspective, to assess the costs and cost-effectiveness of the intervention compared to usual care. Data sources and collection methods for the costs will include project records and surveys conducted throughout the follow-up period, and we will follow the WHO Costit modules to estimate the *costs of delivering the intervention* (start-up costs, staff, training, mobile phone service, cash transfers). We will estimate the average costs per individual in each treatment group throughout the follow-up. The economic evaluation will consist of a cost consequence analysis (CCA) and cost-effectiveness analysis (CEA). Cost consequences will include all outcomes listed in the study objectives. The CEA will focus on the incremental costs per Disability-Adjusted Life Years (DALYs) gained in terms of reductions in stunting.

#### Health-related quality of life (HRQoL)

We will use the WHO-BREF tool at the baseline and end-line data collection. The tool has 26 questions from the WHO-100 QoL questionnaire covering various dimensions, each of which has five levels with categories depending on the type of questions asked.

### Process evaluation

We will conduct a mixed-methods ongoing process evaluation to examine the implementation of the interventions, including delivery of messages, cash and nutrition counselling, to identify the contextual factors that affect the interventions, and to assess the reach of the interventions [42]. We will develop a Program Impact Pathway (PIP) to illustrate the possible routes of achieving the impact of the different intervention elements. The PIP will identify the possible causal links between the interventions and their intended impacts. It includes defining changes, linking processes, and identifying indicators to monitor progress towards the expected impacts. Thus, the PIP will guide the process evaluation data collection. The data will be collected through in-depth interviews and focus group discussions with intervention recipients (mothers of infants, their husbands) and implementers (project officers, managers, and counsellors). We will collect the data longitudinally in three phases. The first phase of data collection will take place within 1 month of the onset of the intervention, while the second and the second and third phases of data collection will be at midline and end-line of the intervention. These methods will generate information about beneficiaries’ response to the intervention, barriers to comply with the nutrition messages and use of cash, and any contextual factors that may influence the outcome. We will also collect information on variations in the accessibility and response to the intervention among the participating households or clusters and underlying factors for the differences will also be collected. In addition to the qualitative data, we will collect quantitative information as part of the regular project monitoring to assess intervention adequacy and reach. We will use the process evaluation data to make necessary adjustments to the intervention and to keep the program ‘on-track’ (formative use) and to interpret and explain outcome results (summative use) at the end of the trial [43].

### Sampling frame and sample size

We require a sample size of 2184 mother-infant pairs (1092 per group) from 104 clusters recruited over 6 months to demonstrate a 6.2% difference in stunting prevalence between treatment groups (40.2% in control to 34.0% in the intervention or 16% relative reduction). The assumed stunting reduction is similar to that observed in a recent study in Bangladesh for face-to-face nutrition BCC plus cash transfers [unpublished data]. Taking account of the potential loses noted below; we would need to recruit 2840 pregnant women to ensure this sample size for the outcome assessment. In this calculation, we used 80% power, a standard two-tailed 5% significance level, a design effect of 1.28 (based on an estimate for stunted children age 12–24 months from the poorest 40% of households in the 2014 BDHS data and an intracluster correlation coefficient (ICC) of 0.0051 assuming a cluster size of 20. This sample size would detect a five-percentage point difference in the prevalence of low birth weight (LBW) between treatment groups with 80% power assuming an ICC of 0.01 and prevalence of LBW of 25% in the control group.

To calculate the estimated sample size, we made several assumptions. We expect the prevalence of stunting (length-for-age < − 2 Z) of 40.2% in control clusters according to latest round of Bangladesh Demographic and Health Survey [4]. Each cluster will have two villages with an average population of 3000. Considering the crude birth rate of 23/1000 population over 12 months [44], we expect that the average number of births will be approximately 34 over 6 months in each cluster. We expect to reach 90% of births though our surveillance system, which means that approximately 31 mother-infant dyads would be available per cluster over 6 months. From our experience in earlier trials, we expect to lose about 10% of pregnancies before birth, 5% of the recruited women will migrate out from the study area and 10% of pregnant women will deliver outside their village. We expect further loses from child deaths in the first 2 years of life.

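### The 2840 recruits are fully used up by the three quantified losses, so the child deaths expected before the 18-month outcome have no effective allowance

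*Protocol article*

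**What the plan says.** All the figures are in the protocol article, section Sampling frame and sample size.

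- Target: "We require a sample size of 2184 mother-infant pairs (1092 per group) from 104 clusters recruited over 6 months".
- Recruitment: "Taking account of the potential loses noted below", the plan continues, "we would need to recruit 2840 pregnant women to ensure this sample size for the outcome assessment".
- Quantified losses: for pregnancy loss, "we expect to lose about 10% of pregnancies before birth". Migration is put at 5% of those recruited, with no stated timing. For place of delivery, the assumption is that "10% of pregnant women will deliver outside their village".
- Unquantified loss: "We expect further loses from child deaths in the first 2 years of life".

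The Trial outcomes section places the primary outcome, stunting, at 18 months of age. Study design gives a follow-up of about 24 months from recruitment. No other rate of loss between birth and 18 months appears. The Comparison arm section says only that differential loss is not expected to be a problem.

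**The concern.** The protocol does more than quote a recruitment number. It says what the number covers (the losses listed below it) and what it secures (2184 pairs at the outcome assessment). Child deaths are among the listed losses and fall between birth and the primary measurement. If the inflation from 2184 to 2840 is already consumed by the other three items, each such death takes the analysed number below 2184, and the stated size is not delivered on the protocol's own assumptions.

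At stake is the power for the primary comparison, which is claimed for 2184 measured children. A second question follows from the same sum. One of the three items, delivery outside the village, is not obviously a loss to a measurement made 18 months later on children of permanent residents. How it is treated decides whether there is a shortfall at all.

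**Working it through.** **Inputs** (Sampling frame and sample size): 2184 pairs required, 1092 per group; 2840 to recruit; losses of 10%, 5% and 10%; stunting 40.2% against 34.0%; two-sided 5% level; design effect 1.28; ICC 0.0051 with cluster size 20.

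**Step 1. Reproduce 2840.** Sequential retention is 0.90 x 0.95 x 0.90 = 0.7695. Then 2184 / 0.7695 = 2838.2. Per group, 1092 / 0.7695 = 1419.1, which rounds up to 1420, and 2 x 1420 = 2840. Conversely, 2840 x 0.7695 = 2185.4, one child above the target before any child death.

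**Step 2. Other ways to reach or read 2840.**
- Additive losses (10 + 5 + 10 = 25%): 2840 x 0.75 = 2130, already below 2184.
- Multiplying by 1.30 (25% plus an unstated 5%): 1092 x 1.30 = 1419.6, which also rounds up to 1420 per group and gives 2840. But a 30% loss from 2840 leaves 2840 x 0.70 = 1988.

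Once child deaths are counted with the three quantified losses, none of these readings leaves 2184.

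**Step 3. Size of the gap.** The rate x of further loss is an assumption, because the documents give none. Children at 18 months = 2840 x 0.7695 x (1 - x). Recruits needed = 2184 / (0.7695 x (1 - x)).

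Power uses the normal approximation with n = children per group / design effect: power = Φ[(d√n - 1.96√(2p̄q̄)) / √(p1q1 + p2q2)], where p1 = 0.402, p2 = 0.340, d = 0.062, p̄ = 0.371 and q = 1 - p throughout. The design effect is either 1 + 19 x 0.0051 = 1.0969 (from the stated ICC and cluster size) or the stated 1.28.

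| Assumed x | Children at 18 months | Short of 2184 | Recruits needed | Power, 1.0969 | Power, 1.28 |
|---|---|---|---|---|---|
| full 2184 | 2184 | 0 | n/a | 81.7% | 75.6% |
| 1% | 2163.5 | 20.5 | 2867 | 81.4% | 75.2% |
| 3% | 2119.8 | 64.2 | 2926 | 80.6% | 74.3% |
| 5% | 2076.1 | 107.9 | 2988 | 79.8% | 73.4% |
| 10% | 1966.8 | 217.2 | 3154 | 77.6% | 71.1% |

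From 3% to 10% further loss, the drop is 1.1 to 4.1 points on the ICC basis and 1.3 to 4.5 points at 1.28. The starting value of 75.6% at 1.28 comes from the conflict between that design effect and the ICC. That is a separate matter and not a consequence of this one.

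**Step 4. If children delivered outside the village are measured at 18 months.** 2840 x 0.90 x 0.95 = 2428. With 5% postnatal loss, 2428.2 x 0.95 = 2307. With 10%, 2428.2 x 0.90 = 2185.

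**The case against.** The strongest reply is that the protocol prints no formula, so a zero allowance for deaths is an inference. The 1.30 multiplier gives exactly 2840 as well and could include 5% for deaths. That is fair as to how the number arose, but that reading leaves 1988, so it does not rescue the claim.

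Three further objections stand and limit the point:

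- A reader might infer that the inflation covers only losses up to delivery. The document does not show this. The 5% migration has no stated timing and could include moves after birth. That 5% is already spent in the 2840, so the sum is unchanged.
- A reader might infer that 2184 children will not be available. That holds only if women who deliver elsewhere are truly lost, and step 4 shows a surplus if they are not. Supply is not capped at 2840 either: about 31 dyads per cluster x 104 = 3224, or about 3063 at the 95% consent given under Recruitment and consent of women.
- A reader might infer that the plan drops these women from the analysis and so introduces bias. Nothing says so. Delivery outside the village appears only as a planning assumption, Statistical analyses specifies intention to treat, and the Comparison arm section provides phone contact to limit differential loss.

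It is also true that most of the distance between 80% and the 71% to 74% figures comes from the design-effect conflict.

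**Conclusion.** The statement that 2840 recruits secure 2184 pairs for the outcome assessment does not hold on the losses the protocol itself lists. The three quantified items exhaust the margin, and the expected child deaths have no effective allowance. The consequence is modest. On the ICC basis, power stays at about 80% for up to 5% further loss and reaches 77.6% at 10%. At the stated design effect, the extra cost is at most about 4.5 points over the same range. These sizes rest on an assumed 1% to 10% further loss and on counting delivery outside the village as a loss, as the protocol does. Neither a certain shortfall nor a biased analysis set follows from the document. Severity is minor to moderate.

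**What to change.** 1. Add an explicit rate for child death and other postnatal loss, and state whether the 5% migration covers the whole follow-up.
2. State whether children delivered outside the village will be measured at 18 months. If so, treat the delivery as a possible missed birth visit and remove that 10% from the losses to the primary outcome. With 5% postnatal loss, the expected number is 2840 x 0.90 x 0.95 x 0.95 = 2307.
3. If they are truly lost, restate the lower number and power from the table. Alternatively, raise the target: 2926 to 2988 recruits for 3% to 5% loss fit within the roughly 3063 consenting dyads, whereas 3154 for 10% do not.
4. Report the expected number and power at 18 months on one stated design effect.

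The cost is a few sentences and one recalculation. If children delivered outside the village are to be measured, it also takes an instruction to trace them for the scheduled 18-month visit. Under item 2, no further enrolment is needed for postnatal loss up to about 10%.

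### The stated design effect (1.28) contradicts the stated ICC and cluster size; at 1.28, 2184 pairs give about 76% power on the primary outcome, not 80%

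*Protocol article*

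**What the plan says.** Under Sampling frame and sample size, the protocol article states: "We require a sample size of 2184 mother-infant pairs (1092 per group) from 104 clusters recruited over 6 months". The target contrast is "40.2% in control to 34.0% in the intervention or 16% relative reduction", a difference of 6.2 percentage points.

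The inputs follow in one sentence: "In this calculation, we used 80% power", then "a standard two-tailed 5% significance level, a design effect of 1.28", the last of which is linked to 2014 national survey data on stunting at 12–24 months in poorer households. The same sentence adds an "intracluster correlation coefficient (ICC) of 0.0051 assuming a cluster size of 20". A bracket opened before the survey reference is never closed, so it is unclear which of these figures the survey supports.

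Losses are handled separately by recruiting 2840 women, so 2184 is the number to be analysed. Cluster recruitment gives equal numbers of clusters per arm, hence 52 and 52.

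**The concern.** Design effect, ICC and cluster size are tied by one formula, so any two fix the third. Here all three are printed as inputs to the same calculation and they disagree. The sample size also does not follow from the printed design effect.

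The claim at stake is the 80% power for the single primary outcome. If 1.28 is the right inflation for this trial, the stated power is too high, and a non-significant result would be read against a power claim that the design does not meet. Anyone reusing the printed clustering figures for a later stunting trial would also have to choose between values that differ almost threefold on the ICC scale.

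**Working it through.** **Inputs** (all from Sampling frame and sample size, except the allocation): control 40.2%, intervention 34.0%, two-sided 5%, power 80%, design effect (DE) 1.28, ICC 0.0051, cluster size m = 20, and 1092 per group in 52 clusters. Note that 2184/104 = 21 per cluster.

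**1. Is 2184 the analysed number?** Applying the listed losses (10% of pregnancies, 5% migration, 10% delivering elsewhere) gives 2840 × 0.90 × 0.95 × 0.90 = 2185. So yes; attrition does not explain what follows.

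**2. Do the clustering figures agree?** DE = 1 + (m − 1) × ICC.
- ICC 0.0051: 1 + 19 × 0.0051 = 1.097 at m = 20; 1 + 20 × 0.0051 = 1.102 at m = 21.
- ICC needed for DE 1.28: 0.28/19 = 0.0147 at m = 20; 0.28/20 = 0.0140 at m = 21.
- Cluster size needed for DE 1.28 at ICC 0.0051: 1 + 0.28/0.0051 = about 56.

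**3. Which design effect reproduces 1092 per group?** The unclustered requirement with unpooled variance is

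n = (1.96 + 0.842)² × (0.402 × 0.598 + 0.340 × 0.660) / 0.062² = 949 per group.

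The pooled-variance form gives 952, and the continuity correction raises these to 981 and 984.

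| Formula | Unclustered n | × 1.28 | × 1.097 | × 1.102 |
|---|---|---|---|---|
| Unpooled | 949 | 1215 | 1041 | 1046 |
| Pooled | 952 | 1219 | 1044 | 1049 |
| Unpooled, continuity-corrected | 981 | 1256 | 1076 | 1081 |
| Pooled, continuity-corrected | 984 | 1260 | 1079 | 1084 |

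Nothing in the 1.28 column comes near 1092. An arcsine version gives 1218, and a one-sided test gives 960. The stated 1092 is 10% below 1215 and 13% below 1260.

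The ICC-based columns come close. With the continuity correction they give 1076 to 1084. By cluster count without the correction, 1044/20 = 52.2, or about 52 clusters per arm, and 52 × 21 = 1092 exactly.

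**4. Power with 1092 per group.** The effective size is 1092/DE.

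| DE | Effective n | Power (pooled z) | Continuity-corrected | t, 102 df |
|---|---|---|---|---|
| 1.097 | 995 | 81.7% | 80.5% | 81.1% |
| 1.102 | 991 | 81.6% | 80.3% | 80.9% |
| 1.28 | 853 | 75.6% | 74.0% | 74.9% |

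The unpooled form gives 75.7% at DE 1.28. There, the difference detectable with 80% power from a 40.2% control rate is about 6.5 points. Reaching 80% for 6.2 points would need 2 × 1219 = 2438 analysed pairs, 254 more than stated.

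**The case against.** The best defence is that the ICC was the real input and 1.28 is a stray figure, perhaps a survey design effect from larger sampling clusters. The numbers favour this reading. The ICC with clusters of 20 to 21 leads to about 52 clusters per arm and close to 1092 children, and power is then 80 to 82%, as claimed. The cluster size is printed next to the ICC, while 1.28 is printed next to the survey reference. On this reading one number is wrong and the trial is adequately powered. That stands as the more likely explanation, and the 76% must therefore be read as conditional on 1.28. It does not rescue the text: 1.28 is listed as an input to this calculation, and nothing else in the article withdraws or explains it.

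Two further points have some force. The loss is modest: about 4 points of power, or 0.3 points of detectable difference. Reading the 16% relative reduction literally (33.8% in the intervention arm) lifts power at 1.28 to 78.6%, though this still needs 1132 per group and the article fixes 34.0%. Also, the Statistical analyses section promises a cluster-adjusted test and confidence interval, so the estimate and its interval will reflect the clustering actually observed. The harm is therefore confined to the stated power and to how a null result is read against it; the validity of the analysis is not affected.

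Nor can the point be left to an unseen analysis plan or put down to the brevity of an article. Nothing is said to be missing; printed figures contradict each other.

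**Conclusion.** The concern holds. The design effect of 1.28 is incompatible with an ICC of 0.0051 at 20 per cluster, and 2184 analysed pairs do not follow from it under any standard formula tried. If 1.28 is right, primary power is about 76% (74 to 76% across methods), and 80% power is reached only for about 6.5 points. If 0.0051 is right, the design effect is 1.10 and power is about 80 to 82%.

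These figures assume equal cluster sizes, the stated 40.2% and 34.0%, and all 2184 pairs analysed. Which input was intended cannot be determined from the article. The likelier reading is that the ICC was used, but only the sponsor can confirm it.

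**What to change.** State one ICC, one cluster size and the design effect that follows from them, and say which of these comes from the survey.

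- **If 1.28 stands:** give the matching ICC (0.0147 at 20 per cluster, 0.0140 at 21) and restate primary power with 2184 analysed as about 76% for 6.2 points, or 80% for about 6.5 points.
- **If 0.0051 stands:** replace 1.28 with 1.10, give the resulting power (80 to 82%) and the formula used, and report the power at 1.28 as a sensitivity figure.

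The cost is a corrected sentence and one recalculation. No change to enrolment, design or analysis is requested. On the first branch the stated power becomes slightly less favourable.

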### Aims and hypothesis

The Shonjibon – Cash and Counselling (SCC) study aims to assess the effectiveness of unconditional cash transfers combined with a mobile application on nutrition counselling and direct counselling through mobile phone in reducing the prevalence of stunting (length-for-age < − 2 Z) in children at 18 months. The primary hypothesis is that in a community-based, cluster-randomised controlled trial of women from food insecure populations, mobile phone-based nutrition behaviour change communications (BCC) and unconditional cash transfers will reduce the prevalence of child stunting at 18 months by 6.2% (40.2% control – 34.0% intervention, or 16% relative reduction) compared to usual programs. The secondary hypotheses are that mobile phone nutrition BCC and unconditional cash transfers compared to the usual programs will: a) increase maternal caloric intake and dietary diversity; b) reduce the rate of low birth weight and small for gestational age newborns; c) improve breastfeeding and complementary feeding practices, including dietary diversity, d) improve women empowerment, and e) be cost-effective in reducing child undernutrition.

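### The 80% power stated for low birth weight matches a calculation without clustering; at the protocol's own ICC of 0.01 it is about 72–73%

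*Protocol article*

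**What the plan says.** The section Sampling frame and sample size first fixes the trial's size on stunting at 18 months: "We require a sample size of 2184 mother-infant pairs (1092 per group) from 104 clusters". The test level given there is "a standard two-tailed 5% significance level", and the assumed cluster size is 20. The same paragraph then adds a power statement for a secondary outcome: "This sample size would detect a five-percentage point difference in the prevalence of low birth weight (LBW) between treatment groups with 80% power assuming". The inputs listed for it are a control prevalence of 25% and an ICC of 0.01.

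The direction of the effect comes from Aims and hypothesis, where secondary hypothesis (b) is that the intervention will "reduce the rate of low birth weight and small for gestational age newborns". The comparison is therefore 25% in control against 20% in the intervention arm. Low birth weight is also part of the first item in the list of secondary outcomes under Trial outcomes.

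**The concern.** A power statement that names an ICC tells the reader that clustering has been allowed for. Here the stated 80% is what an individually randomised trial of the same size would have. Once the named ICC is applied, the chance of missing a true 5-point reduction is about 27–28%, not 20%.

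The risk lies in how a null result is read. If the low birth weight comparison is not significant, a reader who trusts the stated power will take it as stronger evidence against a 5-point effect than the design can supply.

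**Working it through.** **Inputs** (all from Sampling frame and sample size, except the direction of effect, from Aims and hypothesis)

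- Control proportion p1 = 0.25; intervention proportion p2 = 0.20; difference d = 0.05
- Two-sided alpha 0.05 (z = 1.96); power 80% (z = 0.842)
- 1092 per arm; 104 clusters, so 52 per arm and 1092 / 52 = 21 infants per cluster (the text also assumes 20)
- ICC 0.01

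**Step 1. The protocol's figure, ignoring clustering**

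n per arm = (1.96 + 0.842)² × (0.25 × 0.75 + 0.20 × 0.80) / 0.05² = 1091 with unpooled variance, or 1094 with pooled variance under the null.

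The plan has 1092. Power at 1092 per arm with no design effect is 79.9% (pooled), 80.0% (unpooled) and 80.0% (arcsine). This reproduces the stated 80%.

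**Step 2. The same calculation with the named ICC**

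Design effect = 1 + (m − 1) × ICC

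- m = 20: 1 + 19 × 0.01 = 1.19; effective n = 1092 / 1.19 = 918 per arm
- m = 21: 1 + 20 × 0.01 = 1.20; effective n = 1092 / 1.20 = 910 per arm

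| Method (two-sided 5%) | No clustering | m = 20 | m = 21 |
|---|---|---|---|
| Pooled z-test | 79.9% | 72.8% | 72.4% |
| Unpooled z-test | 80.0% | 72.9% | 72.5% |
| Arcsine | 80.0% | 72.9% | 72.5% |
| t reference, 102 df | – | 72.1% | 71.7% |
| Continuity-corrected | 78.5% | 70.9% | 70.5% |

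No two-sided version at ICC 0.01 comes near 80%.

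**Step 3. What 80% would take**

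- Required n at a fixed design effect: 1094 × 1.19 = 1302 per arm, or 1094 × 1.20 = 1313 per arm (1091 × 1.20 = 1309 unpooled).
- With 52 clusters per arm held fixed, a larger m also raises the design effect. Power is 79.6% at 26 infants per cluster and 80.7% at 27 (104 × 27 = 2808 in total).
- With 1092 per arm and design effect 1.20, the difference detectable at 80% power is 5.46 points, that is 25% to about 19.5%.

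**Step 4. Could more infants be available at birth?**

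Starting from the 2840 women to be recruited and removing the listed losses in turn:

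| Infants counted | Total | Per cluster | Design effect | Power |
|---|---|---|---|---|
| All recruits, no losses | 2840 | 27.3 | 1.263 | 81.1% |
| After 10% pregnancy loss | 2840 × 0.90 = 2556 | 24.6 | 1.236 | 77.8% |
| Also after 5% migration | 2556 × 0.95 = 2428 | 23.3 | 1.223 | 76.1% |
| Also after 10% delivering outside the village | 2428 × 0.90 = 2185 | 21.0 | 1.200 | 72.4% |

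The last row returns the planned 2184.

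**The case against.** Four points can be made for the protocol.

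*Low birth weight is measured at birth, so later losses do not apply.* This has some force. The text does not say when migrating women are lost, or that every birth outside the village goes unweighed. But the sentence refers to the stated sample size, which is 2184, and the three listed losses by themselves take 2840 to 2185. Counting every birth after pregnancy loss still gives only 77.8%. Power passes 80% only if pregnancies assumed lost are counted, or if all of the roughly 31 dyads available per cluster take part. The latter gives 84.7%, but 104 × 31 = 3224 exceeds the recruitment target of 2840.

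*The detectable difference may have been rounded.* A clustered calculation gives 5.46 points, which rounds to five. That is possible, but the sentence pairs five points with 80%, and at five points the power is about 72–73%.

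*The cause is inferred.* This stands. The protocol does not show the low birth weight calculation, and 1092 was set for stunting. The match without clustering is close (1091 to 1094 needed, 1092 planned), but it is not proof. The error does not depend on it: however the 80% arose, the stated inputs do not produce it. A one-sided 5% test would give about 82%, but the paragraph specifies a two-tailed level.

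*The consequence is limited.* This also stands. The sentence supports one secondary outcome and does not set the number of clusters, the recruitment target or the analysis. Under Statistical analyses, secondary outcomes are to be modelled with a cluster random effect, so the low power figure does not affect the type I error.

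**Conclusion.** The concern holds. With 2184 infants in 104 clusters and ICC 0.01, power for 25% against 20% is 72.4% to 72.8%, against a stated 80%. The shortfall is about 7 to 8 percentage points. Equivalently, the design detects about 5.5 points at 80% power. The most favourable reading consistent with the protocol's pregnancy-loss assumption (2556 births weighed) gives 77.8%, still below the claim.

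These figures take the protocol's ICC and control prevalence as given and assume equal cluster sizes; unequal sizes would lower power further. That clustering was left out is the likely explanation, not an established one. This is an error in a secondary power statement that should be corrected. It does not bear on the primary sample size.

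**What to change.** Replace the sentence with one that follows from its own inputs. For example: with 2184 births in 104 clusters, an ICC of 0.01 and 25% low birth weight in control, a two-sided 5% test has about 72–73% power for a 5-point reduction, or 80% power for a reduction of about 5.5 points (25% to 19.5%).

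If the sponsor meant a larger number of infants weighed at birth, the sentence should give that number, the resulting cluster size and the power that follows, using Step 4 above as a guide.

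The cost is one sentence and a less favourable figure. The design, recruitment target and analysis need not change.
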